## Abstract

**Introduction:**

There is growing interest in assessing the impact of health interventions, particularly when women are the focus of the intervention, on women’s empowerment. Globally, research has shown that interventions targeting nutrition, health and economic development can affect women’s empowerment. Evidence suggests that women’s empowerment is also an underlying determinant of nutrition outcomes. Depending on the focus of the intervention, different domains of women’s empowerment will be influenced, for example, an increase in nutritional knowledge, or greater control over income and access to resources.

**Objective:**

This study evaluates the impact of the Shonjibon Cash and Counselling (SCC) Trial that combines nutrition counselling and an unconditional cash transfer, delivered on a mobile platform, on women’s empowerment in rural Bangladesh.

**Methods and analysis:**

We will use a mixed-methods approach, combining statistical analysis of quantitative data from 2840 women in a cluster randomised controlled trial examining the impact of nutrition behaviour change communications (BCCs) and cash transfers on child undernutrition. Pregnant participants will be given a smartphone with a customised app, delivering nutrition BCC messages, and will receive nutrition counselling via a call centre and an unconditional cash transfer. This study is a component of the SCC Trial and will measure women’s empowerment using a composite indicator based on the Project-Level Women’s Empowerment in Agriculture Index, with quantitative data collection at baseline and endline. Thematic analysis of qualitative data, collected through longitudinal interviews with women, husbands and mothers-in-law, will elicit a local understanding of women’s empowerment and the linkages between the intervention and women’s empowerment outcomes. This paper describes the study protocol to evaluate women’s empowerment in a nutrition-specific and sensitive intervention using internationally validated, innovative tools and will help fill the evidence gap on pathways of impact, highlighting areas to target for future programming.

**Ethics and dissemination:**

Ethical approval has been obtained from the International Centre for Diarrhoeal Disease Research (Ref. PR 17106) and The University of Sydney (Ref: 2019/840). Findings from this study will be shared in Bangladesh with dissemination sessions in-country and internationally at conferences, and will be published in peer-reviewed journals.

Strengths and limitations of this studyThis paper describes the study protocol evaluating women’s empowerment in a nutrition-specific and nutrition-sensitive randomised controlled trial and will help fill the evidence gap on pathways of impact for women’s empowerment and highlight areas to target for future policy and programming.Formative research guided this mixed-methods approach.We have designed specifically tailored tools, based on a theory of change, and using an internationally validated index that has been piloted in Bangladesh.We are not using the Project-Level Women’s Empowerment in Agriculture Index in full as we interview women only for the quantitative component and will not calculate the Gender Parity Index, which is an index that sheds light on the sense of intrahousehold inequality; however, we will explore this with qualitative research.

## Background

To define women’s empowerment is not straightforward, nor is it easy to measure across the different domains and phases of a woman’s life. Empowerment is ‘the process of enhancing an individual’s or group’s capacity to make purposive choices and to transform those choices into desired actions and outcomes’.^1^ The United Nations defines women’s empowerment as having five key components: ‘women’s sense of self-worth; their right to have and to determine choices; their right to have access to opportunities and resources; their right to have the power to control their own lives, both within and outside the home; and their ability to influence the direction of social change to create a more just social and economic order, nationally and internationally’.^2^

Gender, socially constructed roles assigned by sex, is one of the keynote determinants of health outcomes,^3^ making gender equality and the rights of women an imperative goal in global public health. Gender inequality and restrictive gender norms are, according to the Lancet 2019 series on Gender Equality, Norms and Health, ‘powerful but separate determinants of health and well-being’.^3^ Sustainable Development Goal (SDG) 5 aims to achieve gender equality and to empower all women and girls, ending discrimination in all forms, from violence to forced marriage, and experience full active participation and equal rights in all spheres of life—politically, economically and socially.^4^ Out of the 17 SDGs, 11 entail indicators related to gender.

Much progress has been made towards gender equality and the empowerment of women globally. Yet, the potential for women to fully participate as ‘agents of change’ is still limited due to persistent social, economic and political inequalities.^5^ Women continue to be constrained by norms, beliefs and customs through which societies differentiate between women and men.^6^ Contextual forms of oppression include patriarchal societies and institutions, as well as lack of opportunity due to socioeconomic circumstances such as poverty. Violence, including intimate partner violence (IPV), disproportionally affects women. Worldwide, a third of women report experience physical or sexual IPV.^7^ Women subjected to IPV suffer poor mental and physical health, and their children show poorer health, nutrition and development outcomes.^8^ Evidence suggests that the combination of cash transfers and behaviour change communication (BCC) can increase women’s bargaining power and poverty-related emotional well-being and can lead to a reduction in IPV.^8^

Interventions to improve the health and nutrition literacy of women and, in particular, counselling through mobile phone applications can make a positive impact on women’s empowerment. Mobile health (mHealth) interventions have the potential to improve a woman’s confidence and decision-making skills in communicating with healthcare professionals. However, a systematic review revealed the need for a further rigorous investigation into mHealth, in terms of implementation and evaluation, to establish whether mHealth programmes transform rather than reinforce gender inequalities.^9^ When a woman receives additional resources, such as cash transfers, and is the target of an mHealth programme, this can challenge gender norms within relationships and exacerbate gender disparities.^9^ There is limited evidence on the adverse effects of mHealth, such as expanding the digital divide and gender-based power imbalances, and this lack of evidence emphasises the need to monitor the impact of mHealth interventions on gender relations and women’s empowerment.^9^

The Lancet Series on Maternal and Child Nutrition also advocates the use of cash transfers and social safety net programmes, which are increasingly the preferred approach to support households living in chronic and extreme poverty.^10^ When targeted at women, social protection can promote women’s economic empowerment and enhance decision-making ability, with the overarching assumption that control over cash will lead to greater investment in children’s health and education.^10 11^ When women are engaged in nutrition-sensitive programmes that use social safety nets, certain aspects of women’s empowerment are augmented, such as changes in gender roles and intrahousehold bargaining power.^10^

We plan to conduct a study, embedded in a cluster randomised control trial (RCT) that assesses a multifaceted nutrition intervention that aims to reduce childhood stunting—the Shonjibon Cash and Counselling (SCC) Trial.^12^ This protocol paper presents the way we will measure the impact of the SCC Trial on women’s empowerment.

### Developmental interventions and women’s empowerment in Bangladesh

Although Bangladesh has made remarkable reductions in rates of poverty, almost one in four of the population still live in poverty (24.3% in 2016).^13^ In 2018, the agriculture sector accounted for 40% of total employment.^14^ In most low-income countries, women account for almost half of the agricultural labour force; however, in Bangladesh, women exceed 50% of the agricultural labour force.^15^ In rural Bangladesh, social constructs such as gender roles of women and men powerfully drive household food consumption.^16^ A nationally representative sample from Bangladesh found that women’s empowerment increases dietary diversity and availability of calories at a household level.^17 18^ The Government of Bangladesh and development organisations have shown a keen interest in combining nutrition counselling and cash transfers to improve maternal and child nutrition.^19^

In rural Bangladesh, 84% of households have access to a mobile phone.^20^ A study in Bangladesh revealed women using Aponjon, a mobile messaging-based service providing information about mother and babies, had higher rates of autonomy in accessing mobile phones, although two-thirds of the women resided in urban areas. mHealth consultations may help address sociocultural gender norms and empower women as they were able to discuss personal health issues on the phone with female doctors who are infrequently found in rural communities.^20^ The need to collect sex-aggregated, valid, comprehensive and standardised empowerment data is therefore imperative not only to achieve SDG 5 but also to enable the consistent measurement of women’s empowerment indices.^21 22^

### Objectives and hypotheses

This study evaluates the impact of a combined nutrition counselling and an unconditional cash transfer RCT (SCC Trial), delivered on a mobile platform, on the level of empowerment of women in rural Bangladesh. This study will assess women’s experience of empowerment and disempowerment throughout the SCC trial.

The primary hypothesis is that in a community-based cluster RCT of a mobile phone-based nutrition BCC and unconditional cash transfer given to women in low-income families in rural Bangladesh, women’s empowerment will increase as measured by an increase in mean women’s empowerment scores (by an average percentage of 20) from the baseline to the end of the 24-month intervention, compared with women in the control arm.

The secondary hypotheses are that the mobile phone nutrition BCC and unconditional cash transfer compared to usual programmes will (1) increase control over income and economic resources, (2) improve input and decision-making power in nutrition and health care choices, and (3) decrease the acceptance and experience of IPV.

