### Study outcomes

The primary study outcome will be the difference in women’s empowerment scores in the intervention arm as compared with the control arm of the SCC Trial. Secondary study outcomes will include (1) control over income and economic resources, (2) input and decision-making power in nutrition and healthcare choices, and (3) experience and attitude towards IPV.

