### Sample size and power

The sample size for our trial is fixed by the primary hypothesis in the main SCC Trial, which estimated a total sample of 2184 mother–infant pairs from 104 clusters.^12^ We can find no reports of intracluster correlation coefficients (ICCs) for the women’s empowerment indicators we plan to use. Therefore, we estimate that the fixed trial sample size will provide at least 80% power to detect a 20% increase in women’s empowerment, assuming 30% of women are empowered and a high ICC of 0.2. Assuming a lower ICC of 0.05, we will have 90% power to detect a 13% increase in women’s empowerment.

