### Quantitative data analysis

Data analysis will be by intention to treat. The women’s empowerment composite index scores will be categorised as the percentage of women as empowered or disempowered. For each empowerment indicator, individuals are classified as adequate or inadequate based on Pro-WEAI predetermined thresholds. Women are considered empowered if four out of six indicators are adequate. We will also analyse impact of SCC intervention on individual indicators to assess increases or decreases in empowerment as not all indicators will respond or be impacted in the same way.

Analyses will be conducted at the mother–infant dyad level but will be adjusted for the cluster randomisation.^39^ Primary analyses will compare the prevalence of women’s empowerment at the end of the trial using Pearson’s χ^2^ tests and 95% CIs for the group difference, adjusted for clustering and generalised linear mixed models for non-continuous outcomes (eg, logistic mixed models for binary outcomes, for example, percentage of women’s empowerment). Models will include treatment group as a fixed effect, infants as a random effect to account for repeated measurements, and community cluster as a random effect to account for cluster effects. We will also assess if the women’s empowerment level at baseline, age, education, and presence or absence of a mother-in-law in the household modify the empowerment response to the intervention by testing for interactions between the intervention and these factors. STATA will be used for all analyses.

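### The primary analysis (prevalence of empowered women at the end of the trial) does not test the primary hypothesis (rise in mean empowerment score from baseline)

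*Protocol article*

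**What the plan says.** Four sections of the protocol article describe the primary endpoint.

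- **Objectives and hypotheses.** The primary hypothesis is "an increase in mean women’s empowerment scores (by an average percentage of 20) from the baseline to the end of the 24-month intervention", relative to control. The variable is a mean score and the contrast is change from baseline.
- **Study outcomes.** "The primary study outcome will be the difference in women’s empowerment scores in the intervention arm as compared with the control arm". This says neither mean nor category, and gives no time point.
- **Sample size and power.** The calculation is for a proportion, "assuming 30% of women are empowered and a high ICC of 0.2", and claims "at least 80% power to detect a 20% increase in women’s empowerment". A second claim is 90% power for a 13% increase at an ICC of 0.05. No time point, cut-off or scale (points or relative) is given.
- **Quantitative data analysis.** "The women’s empowerment composite index scores will be categorised as the percentage of women as empowered or disempowered", and "Women are considered empowered if four out of six indicators are adequate". Then: "Primary analyses will compare the prevalence of women’s empowerment at the end of the trial". The models include "infants as a random effect to account for repeated measurements", although the comparison just named is at a single time point. The section also plans analyses of the individual indicators, but none of the mean score.

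**The concern.** A primary analysis should estimate the quantity named in the primary hypothesis. Here the variable differs (mean score against proportion above a cut) and so does the contrast (change from baseline against endline). The figure of 20 appears in both the hypothesis and the power section as if it were one effect, but nothing links the two scales.

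At stake is whether the trial's main claim can be judged. A difference in prevalence neither confirms nor refutes a 20 rise in mean score. The power statement supports the prevalence comparison only. Power for the mean-score hypothesis cannot be worked out, because the article gives no mean or SD for the score.

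**Working it through.** **1. The two measures can move apart.** The score is the number of adequate indicators, 0 to 6, and a woman is empowered at 4 or more.

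- If 20% of women go from 1 to 3 adequate indicators, the mean rises by 0.20 × 2 = 0.40 and prevalence does not change.
- If 20% go from 3 to 4, the mean rises by only 0.20 × 1 = 0.20 and prevalence rises by 20 points.

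**2. The two 20% targets on one scale.** This is an illustration under assumptions that are not in the article: six equally likely indicators driven by correlated normal variables (correlation 0, 0.2 or 0.5), with the threshold set so that 30% of women have at least four adequate. The 30% is the article's own figure.

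| Latent correlation | Mean score at 30% empowered | Prevalence after a 20% relative rise in mean | Relative rise in mean at 36% empowered | Relative rise in mean at 50% empowered |
|---|---|---|---|---|
| 0 | 2.856 | 48.5% | 6.9% | 21.6% |
| 0.2 | 2.639 | 43.1% | 9.5% | 29.8% |
| 0.5 | 2.358 | 39.4% | 13.0% | 41.7% |

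A 20% relative rise in mean is thus a gain of 9.4 to 18.5 points in prevalence. It matches neither 20 points (50%) nor 20% relative (36%).

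**3. The article's power figures.** Inputs: 2184 pairs in 104 clusters, so 1092 per arm and m = 21; 30% empowered; ICC 0.2 or 0.05. Two-sided alpha of 0.05 is assumed, since the article mentions only 95% CIs.

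Design effect = 1 + (m − 1) × ICC:

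- ICC 0.2: 1 + 20 × 0.2 = 5.0, so 1092 / 5.0 = 218.4 effective women per arm.
- ICC 0.05: 1 + 20 × 0.05 = 2.0, so 1092 / 2.0 = 546 per arm.

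Power for an endline comparison of two proportions = Φ[(d − 1.96 × SE0) / SE1], with SE0 pooled and SE1 unpooled.

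- ICC 0.2, 30% v 50%: SE0 = √(2 × 0.40 × 0.60 / 218.4) = 0.0469; SE1 = √((0.21 + 0.25) / 218.4) = 0.0459; power 99.1%.
- ICC 0.2, 30% v 36%: power 26.5%.
- ICC 0.05, 30% v 43%: power 99.4%.
- ICC 0.05, 30% v 33.9%: power 28.2%.

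The claim of at least 80% holds as a lower bound if the 20% means points, and fails if it is relative. The 90% for 13% is not reproduced by an endline comparison on either reading.

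For a change-from-baseline contrast on the same proportion, taking the two waves as independent, SE = √((3 × 0.21 + p2(1 − p2)) / n), where n is the effective number per arm:

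- ICC 0.05, p2 = 0.43: SE = √(0.8751 / 546) = 0.0400; power Φ(0.13 / 0.0400 − 1.96) = 90.1%.
- ICC 0.2, p2 = 0.50: power 88.3%.

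The 90.1% agrees with the stated 90%, but the article does not say that this method was used. The time contrast behind the power figures is therefore unclear. The other sample sizes implied elsewhere (2840, or 104 × 20 = 2080) give 99.0% to 99.7% for the two endline percentage-point comparisons and do not alter the point.

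**4. The model.** With one endline record per woman, a person-level random effect has no repeated measurements to account for. If both waves were meant to enter, a time term and a treatment-by-time term would be needed, and neither is listed.

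**The case against.** The best defence is that the analysis section resolves the matter. It turns the score into a category, fixes the cut and labels only one comparison primary. The power section uses the same kind of quantity, and the outcomes section, which says scores without saying mean, is compatible with it. The hypothesis could then be loose wording for percentage empowered. This is a fair guide to what was probably intended, and it is why the remedy keeps prevalence. It does not remove the conflict: the hypothesis explicitly names a mean and a change from baseline, and no section says which definition governs. Nor is this detail that an analysis plan would ordinarily supply, since both versions are stated.

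On the time contrast, randomisation gives an endline difference and a difference in change the same expectation on a difference scale. That mismatch is the lesser one; the mismatch of variable is the heavier.

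A reader might go further and infer that success could be claimed on whichever outcome comes out better. If both were tested at 5%, the chance of at least one false positive would be about 7.5–7.9% under the illustrative model above. The article does not support this: no section lets either outcome count as success. That error rate describes a departure from the plan. Similarly, the chi-square test and the logistic mixed model address the same binary outcome and are not two endpoints. Loss of information from dichotomising is an argument for a different endpoint, not evidence of a contradiction.

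**Conclusion.** Wrong as written. The stated primary analysis does not answer the stated primary hypothesis, and the target of 20 cannot be judged from the planned result. This follows from the text alone. The size of the gap between the two targets (39–48% prevalence for a 20% rise in mean, against 36% or 50%) rests on the illustrative model and on reading the hypothesis as a relative rise. The undefined scale matters in its own right: for the 20% at an ICC of 0.2, endline power is 99.1% or 26.5% depending on the reading. The finding does not extend to inflated type I error or to a planned choice between endpoints.

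**What to change.** - **Objectives and hypotheses, and Study outcomes:** define the primary outcome as the between-arm difference in the percentage of women empowered (at least four of six indicators adequate) at endline.
- **Objectives and hypotheses, and Sample size and power:** state whether the 20%, and in the power section the 13%, are percentage points or relative. Say which contrast the power figures assume.
- **Quantitative data analysis:** name the cluster-adjusted logistic mixed model as the single primary analysis, with baseline empowerment status as a covariate in place of the repeated-measurement random effect. Report the difference in percentage points with its 95% CI, and label the chi-square test supportive.
- **Secondary outcomes:** add the mean number of adequate indicators.

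Making the mean score primary instead would be a legitimate choice, but it would need a mean, SD and ICC that the article does not have.

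Cost: wording only. Baseline and endline data are already planned, so no new data are needed. The change should be made before outcome data are examined.

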### SCC Trial: women’s empowerment theory of change

Empowering women is not an explicit goal of the SCC Trial; however, women gain access to nutrition counselling, cash transfers and a mobile phone; the use of these resources can empower women. We constructed the theory of change to illustrate how the SCC Trial will impact on women’s empowerment outcomes. It outlines the barriers, intervention details, intermediate outcomes, outcomes and impact pathways (figure 1).

**Figure 1 F1:**
[figure not shown]
SCC Trial: women’s empowerment theory of change (adapted from De Silva *et al*^50^). BCC, behaviour change communication; IYCF, infant and young child feeding; SCC, Shonjibon Cash and Counselling.

The SCC Trial intervention is delivered on a mobile platform. Women receive an mHealth interactive app—messages, audio and video, quizzes—as well as gestational age specific counselling from the call centre. They also receive cash via BKash mobile banking app. The principal rationale of the theory of change causal pathway to impact is that the SCC Trial will lead to an increase in women’s empowerment for those women participating in the intervention arm.

The Project-Level Women’s Empowerment in Agriculture Index (Pro-WEAI)^21^ indicators, discussed in detail later, appear in the theory of change across the outcomes. We will use the six indicators from the Pro-WEAI to calculate the women’s empowerment index and include (1) control over use of income, (2) input into productive decisions, (3) autonomy in income, (4) decision-making power on nutrition and healthcare, (5) respect among household members and (6) attitudes towards IPV.

One of the barriers to nutrition faced in rural Bangladesh is limited access to nutrition and infant and young child feeding (IYCF) information. Women in the SCC Trial intervention arm receive nutrition, IYCF and livelihood BCC delivered on a mobile app and nutrition counselling from the call centre. The intermediate outcome is woman’s acquisition of new BCC/nutrition knowledge, contributing to increased input into and decision-making power about health and nutrition choices for herself and her family (indicator 4). Improvements in communication also occur (spousal, intrahousehold and community) as new knowledge is discussed and shared, including ways to put the messages into action (indicator 5). One’s ability to make decisions is a measure of empowerment.^23^ New knowledge can be used as leverage and bargaining power and enhance decision-making abilities across a range of areas such as livelihoods, household expenditure and decisions on productive assets, that is, what crops to farm (indicators 2–4).

The SCC Trial setting is in one of the poorest regions in Bangladesh. Families face barriers such as food insecurity and lack of financial resources. When a woman is the recipient of a cash transfer, the intermediate outcome is increased control over the use of income (indicator 1). Cash transfers, targeted at women, have the potential to improve livelihoods, alleviate poverty, enhance food security and increase women’s empowerment.^10^ Spousal communication is also strengthened as discussion ensues as to how to spend the additional income (indicator 4). The outcomes for women receiving an unconditional cash transfer include a strengthened ability to contribute to and participate in financial decision making. This decision making covers health and nutrition choices, household expenditure, productive assets, livelihood choices (ie, homestead gardening, buying chickens to raise for eggs, meat and income; indicators 1–4).

IPV includes behaviour that is physical, psychological, sexual, or abusive or controlling in nature.^24^ There is evidence that the combination of additional income from cash transfers combined with BCC can increase women’s bargaining power and poverty-related emotional well-being.^8^ Changing attitudes, from within the family unit, as women participate and learn from intervention activities, has the potential to lead to a change in the acceptability of IPV, linked to a woman’s right to bodily integrity.^25^ Women may also experience an increase in respect and self-efficacy and subsequent reduction in acceptance of IPV (indicator 6).

